## Abstract

**Background**: Evidence shows that physical exercise promotes preschoolers’ fundamental movement skills (FMSs) and physical fitness (PF). However, studies that assess the effectiveness of different types of physical exercise interventions to improve FMSs and PF in preschool children remain scarce. To explore and compare the effectiveness of different physical exercise on FMSs and PF, interventions comprising ball games (BGs), rhythm activities (RAs), basic movements (BMs), and a combination of all related activities (multiple activities, MAs) will be conducted among preschoolers. **Methods**: A single-blind, five-arm, cluster-randomized trial will be conducted in kindergarten in Shanghai, China. In total, 300 healthy preschoolers, aged 4 to 5 years, will be randomized to four intervention groups (BG, RA, BM, or MA) and one control group (unorganized physical activities). Four intervention groups will receive three 30-min lessons weekly for 16 weeks. At the baseline, the end of the 16-week intervention, and the 6-month follow-up after the end of the intervention, the primary outcomes (FMSs and PF) and physical activity (PA), and sociodemographic and anthropometric data will be assessed. **Discussion**: This study will provide vital information regarding the effect of different physical exercise interventions on preschool children’s FMSs and PF, PA, and the potential interactions between these domains. The most effective intervention strategy can be generalized to kindergarten and other preschool educational institutions in practice to promote preschoolers’ development of FMSs and PF. **Conclusions**: This study protocol aims to provide a method to solve the problem of “how to arrange physical exercise and which kind of physical exercise program can promote FMS and PF better in preschool children”.

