
In China, young children (3–6 years old) population is 57 million, 81.7% of whom were enrolled in kindergarten in 2018. Children spend approximately 40 h each week in kindergarten [36]. However, there is little empirical evidence showing the effect of physical exercise on preschoolers’ FMSs and PF in China. Above all, the present trial is designed to respond to the theoretical and evidence gap. Therefore, the aims of this trial are to (1) determine the effectiveness of each of these physical exercise interventions in improving preschool children’s FMSs and PF; and (2) establish the differences between the effectiveness of different physical exercise programs on preschool children’s FMSs and PF. The research hypothesis is that physical exercise interventions will improve children’s FMSs and PF more than unorganized activities, and that MA will show larger beneficial effects than BA, RA, or BM on children’s FMSs and PF.

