## 2. Methods

### 2.1. Study Design

The study is a single-blind, cluster-RCT study, with the kindergarten class as the cluster for the intervention. This study is a part of the Physical Exercise on FMSs and PF of preschoolers (PEFP) project. The PEFP project is a series of studies, including a cross-sectional survey (covering six provincial and municipal regions in China) and the aforementioned RCT (implemented in Putuo District, Shanghai, China). Preschoolers recruited from 5 kindergartens will be cluster-randomly allocated to 5 groups (i.e., four intervention groups and one control group). The intervention groups are (1) the BG group, consisting of football, basketball games, etc.; (2) the RA group, including cheerleading, rhythm exercise, etc.; (3) the BM group, consisting of different basic movements, such as walking, running, jumping, climbing, throwing, catching, etc.; and (4) the MA group, combination of all kinds of physical exercise that have been used in other intervention studies. The control group (control) is an unorganized PA group (Figure 1). The content of the intervention comes from previous research combined with consultation and interviews with preschool educators [7,37].

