## 3. Interventions and Procedures

### 3.1. Intervention Groups

#### 3.1.1. Development of Interventions

The intervention procedures have been developed by (1) applying the framework of exercise programs proposed by the American College of Sports Medicine (ACSM) [38]; (2) constructing domain-specific content for physical exercise interventions via a review of the existing literature for young children [7,26,27,31,37]; (3) obtaining open-ended responses concerning how preschool children exercise to improve FMSs and PF from preschool education experts and teachers; (4) constructing the actual intervention procedures; and (5) examining the validity of factor structures underlying the intervention procedures by consulting other preschool education experts and teachers and conducting pilot studies.

A review of previous studies shows that physical games (aerobic games, ball games, etc.), rhythmic activities, sports (basketball, football, swimming, etc.), fundamental movements activity (gross motor movements, functional movements, etc.), aerobic training, and comprehensive physical exercise were used in FMSs and PF intervention programs for children aged 4–5 years, and proved to be superior to free play or unorganized physical activity [25,29,31]. The results of interviews with preschool education experts and teachers, and the restrictions of the Ministry of Education of the Chinese government on the implementation of standardized “curriculum” and competitive sports in kindergartens were considered [39]. Ball games, rhythmic activities, basic movements, and multiple activities are the physical exercise programs of this study.

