#### 3.1.2. Contents of Interventions

Each of the four interventions is based on structured lessons, which will involve a 30-min lesson three times per week for 16 weeks. In all four groups, each lesson will consist of a 5-min warm-up, 20 min of core exercises, and a 5-min cool-down activity. The warm-up will consist of light-intensity movements (e.g., wrist rotation and leg swing), moderate-intensity activities (e.g., arm rotation and knee-up walk), and higher-intensity activities (e.g., arm sprint and on-site running); cool-down will start with moderate-intensity activities and end with light-intensity movements. The main part of the lesson will include 5 min of moderate-to-vigorous intensity activity according to the respective intervention procedures, with at least 2 min of vigorous-intensity activity, every 10 min [40,41]. The four interventions will be carried out in the form of games to increase children’s interest, and will only differ in the main part (Table 1). The intervention will be carried out within the PA plan of kindergartens, to avoid extra PA for the preschool children in the intervention groups.

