**Figure 2 ijerph-19-06331-f002:**
[figure not shown]
Flow of the assessments of measures in the trial.

**Table 1 ijerph-19-06331-t001:** Description of the contents, specific focus, and time allocation of the four interventions.

Interventions	Specific Focus	Themes	Contents	Lessons Needed
Basic movements	Aims to help preschool children learn and master FMSs, and improve muscular strength, coordination, and sensitivity.	Stable skiers (aiming at stability skills)	Standing and walking	10
		Happy little animals (locomotor skills)	Climbing and running	10
			Jumping	10
		Little ball players (object control skills)	Throwing/catching a ball	6
			Slapping ball	6
			Rolling, kicking, and dribbling	6
Ball games	Enable children to learn and master the basic ball skills, and at the same time promote children’s fitness level.	Rubber ball games	Running/jumping with ball	1
			Rolling pass, throwing, and catching	6
			Slapping and pitching	5
		Basketball games	Slapping basketball	2
			Dribbling	3
			Passing and catching	4
			Throwing, catching, and shooting	4
		Football games	Kicking, stepping over	7
			Dribbling and small-sided games	5
		Tennis games	Tapping	2
			Throwing and catching ball	6
			Hitting fixed ball	3
Rhythmic activities	Develop rhythmic gymnastics, aiming to improve physical control, aerobic fitness, and shaping grace posture.	Animal imitation exercise	Learning basic posture	4
			“I’m a little pacesetter”	12
		Baby warm-up exercise	Basic and jump steps, and body wave	8
		Pizza	“Little swan”	12
		Cheering on	Flower ball cheerleading	12
Multiple activities	Integrates theme activities into physical exercise to cultivate children’s interest and habits regarding regular exercise	Traditional Chinese games	Throw handkerchief games	4
			Beanbags, jumping rope, bench and coin games, etc.	8
		Animal imitation	Hawks Catch chicken, etc.	12
		Role playing and cooperative practice	Pushing cart game, etc.	12
		Military games	Brave little soldiers, etc.	12

**Table 2 ijerph-19-06331-t002:** The Fundamental Movement Skills Tests.

FMS Proficiency	Test	Materials and Site Layouts	Directions	Performance Records	Cautions

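### The MA arm is described as a combination of all activity types, but its 48 lessons in Table 1 name no ball-game or rhythm lesson, so an MA result cannot be read as the effect of combining types

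*Protocol article*

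**What the plan says.** The protocol article describes the multiple-activities (MA) arm in four places.

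- Abstract: after listing ball games, rhythm activities and basic movements, it adds "a combination of all related activities (multiple activities, MAs) will be conducted among preschoolers".
- Section 2.1: "the MA group, combination of all kinds of physical exercise that have been used in other intervention studies". Section 3.1.1 reports what the authors' review found those studies to have used; its list includes "physical games (aerobic games, ball games, etc.), rhythmic activities, sports (basketball, football, swimming, etc.), fundamental movements activity".
- Section 1 states the hypothesis for the arm: "MA will show larger beneficial effects than BA, RA, or BM on children’s FMSs and PF". 'BA' appears to be the ball-game arm, called BG elsewhere.
- Table 1 gives the MA focus as "Integrates theme activities into physical exercise to cultivate children’s interest and habits regarding regular exercise" and allocates lessons to four themes: traditional Chinese games, animal imitation, role playing with cooperative practice, and military games.

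Section 3.1.2 fixes the schedule for every intervention arm at "a 30-min lesson three times per week for 16 weeks". It also says that the four programmes differ only in the main part of the lesson, and refers to Table 1 for that part.

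**The concern.** The text describes MA as a mixture, and on either wording one would expect ball and rhythm content in it. The Abstract's wording reads most naturally as BG, RA and BM together. The wording in section 2.1 points to the literature, and the list in section 3.1.1 includes the same three types. Table 1, which sets out what is taught, names neither ball games nor rhythm work for MA. It presents a separate programme of traditional and themed games.

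What is at stake is the meaning of an MA result. The second aim in section 1 is to compare the programmes with one another, and the Abstract intends the most effective strategy to be taken up in kindergartens. A reader relying on the Abstract and section 2.1 would take a good or poor MA result as evidence for or against mixed programmes. The arm as listed does not supply that evidence.

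The mismatch also touches a primary outcome. Two of the three object-control tests in Table 2 are bouncing a ball and kicking. Table 1 names slapping, dribbling and kicking lessons under BG and BM, and none under MA. An arm that did combine the types would be expected to include some such practice.

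**Working it through.** **1. Is Table 1 the whole programme, or could ball and rhythm lessons lie outside it?**

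Lessons implied by section 3.1.2: 3 per week × 16 weeks = 48.

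Lessons in Table 1, summed by arm:

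- BM: 10 + 10 + 10 + 6 + 6 + 6 = 48
- BG: 1 + 6 + 5 + 2 + 3 + 4 + 4 + 7 + 5 + 2 + 6 + 3 = 48
- RA: 4 + 12 + 8 + 12 + 12 = 48
- MA: 4 + 8 + 12 + 12 + 12 = 48

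All four sums reproduce the planned 48. The MA rows use up the schedule, so no unlisted lessons remain to carry the other types.

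**2. What do the MA rows name?**

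| Theme in Table 1 | Named contents | Lessons |
|---|---|---|
| Traditional Chinese games | handkerchief games | 4 |
| Traditional Chinese games | beanbags, rope, benches, coins, etc. | 8 |
| Animal imitation | a hawk-and-chicken game, etc. | 12 |
| Role playing and cooperative practice | a cart-pushing game, etc. | 12 |
| Military games | a little-soldiers game, etc. | 12 |

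By theme this is (4 + 8) + 12 + 12 + 12 = 48. No row names a ball game, football, basketball, tennis, rhythmic gymnastics or cheerleading.

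**3. How firm is that count?**

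Four of the five rows end in 'etc.' and cover 8 + 12 + 12 + 12 = 44 of the 48 lessons. They give examples, so the table supports the statement that no ball-game or rhythm lesson is named. It does not support a measured share of zero.

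**4. Nearest overlaps with the other arms**

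- Animal imitation: 12 of 48 lessons (25%). RA has a theme with almost the same name, but its contents are basic posture and a named routine.
- The beanbag, rope, bench and coin row: 8 of 48 lessons (17%). Rope jumping is close to BM's jumping lessons.

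These are incidental overlaps of theme or movement. They do not make the listed lessons a combination of BG, RA and BM.

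**5. Description and content side by side**

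| Source | What MA is | Ball and rhythm content expected or named? |
|---|---|---|
| Abstract | combination, listed after BG, RA and BM | expected |
| Section 2.1 with section 3.1.1 | combination of kinds used in earlier studies | expected |
| Table 1 | themed and traditional games | not named |

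The check does not depend on alpha, power, effect size or sample size.

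**The case against.** The strongest defence is that the stated hypothesis says only that MA will do better than the other three programmes. It does not say that combining activities is what works. That comparison can be made on the arms as delivered. A reader might infer that the trial cannot test its hypothesis; the protocol does not support that, and this part of the defence stands.

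A second defence is that section 2.1 takes its reference set from the literature, not from the other three arms. Section 3.1.1 lists comprehensive exercise as a type and names multiple activities as a programme in its own right. Section 1 cites a study in which programmes of varied form and function had advantages over rhythmic gymnastics and football. A varied set of games fits that rationale. This stands in part: it makes Table 1 a plausible programme, but the same list in section 3.1.1 includes ball games and rhythmic activities, and the Abstract's wording is left unexplained.

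Third, Table 1 may be a summary. Section 3.2.1 mentions an intervention portfolio, files and videos that are not shown, and most MA rows are open-ended. This limits how exactly the content can be counted, but the themes and lesson numbers are fixed in the table, and the themes are not those of BG or RA.

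Fourth, the primary analysis in section 4.4 compares each programme with control, and no estimate there changes with the arm's label. This is correct. The point concerns what an MA estimate may be said to show.

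A reader might also see a fault in the ball-skill lessons within BM. They are no error: section 2.1 openly includes throwing and catching in BM, and nowhere does the protocol present BM against BG as no ball against ball.

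**Conclusion.** The description of MA in the Abstract and section 2.1 does not match its content in Table 1. All 48 scheduled lessons are allocated to four themes of 12 lessons each, and no ball-game or rhythm lesson is named among them. MA against BG, RA, BM or control remains a valid comparison of the programmes as delivered. The result cannot be read as the effect of combining the other activity types.

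This rests on two assumptions: that Table 1 is the operative lesson plan, as the reference to it in section 3.1.2 implies, and that the open-ended rows do not conceal substantial ball-game or rhythm teaching. If the unseen lesson materials show otherwise, the table is what needs correcting. The protocol does not show which version is intended. The weight is moderate: the design, sample size and stated primary analysis are untouched, but the interpretation of one of four intervention arms, and of any recommendation built on it, is affected.

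**What to change.** Reconcile the Abstract, the hypothesis in section 1, the arm definition in section 2.1 and the MA row of Table 1 before lessons start. There are two routes, and the choice belongs to the investigators.

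- If Table 1 stands: describe MA as a programme of traditional and themed games, remove the statements that it combines all activities or all kinds of exercise, and word the hypothesis as that programme against BG, RA and BM. State that the MA contrasts do not test combining BG, RA and BM.
- If the combination definition stands: bring the MA row of Table 1 into line with it, so that the listed lessons show which types are combined and how many lessons each receives.

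The first route changes wording only; its price is a narrower claim for the MA arm. The second requires revising the MA lesson allocation within the existing 48 lessons and keeps the broader claim. Once lessons have been delivered, only the narrower claim is available for the arm as listed.

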## 1. Background

Preschoolers are in a critical time of acquiring and consolidating fundamental movement skills (FMSs) [1] and developing physical fitness (PF) [2], which is essential to becoming physically active, less sedentary [3], and achieve health-related benefits both in the near future and in the long term [4,5,6].

Fundamental movement skills are defined as basic learned movement patterns that do not happen naturally and are the foundation of more advanced, complex movements required to participate in context-specific physical activities or sports [4,7]. FMSs include three domains: (1) locomotor skills, which involve locomotion of the body, e.g., running, jumping, etc.; (2) object control skills, which are mainly manipulative skills, e.g., throwing, catching a ball, etc.; and (3) stability skills, including static and dynamic balance [8]. Proficient FMSs may benefit children’s PF [9], weight status [6], social and cognitive capacity [10,11], and have other health-related benefits [12], and enable children to participate in physical exercises [5,13]. However, the evidence from previous study shows that 4.4% of young children (3–6-year-old) showed delayed development of FMSs and 8.8% were at risk of delay [14], and young children are struggling to achieve the recommended level of daily physical activity (PA) [15].

Physical fitness is a multifaceted construct involving physical and physiological components, including cardiorespiratory endurance, strength, speed, reaction, agility, balance, coordination and flexibility, etc. [16], and support individuals’ physical behavior, life, and work with vigor [9,17]. Research has proved that improvement of PF is important for the health of preschool children, particularly for obesity prevention [18]. Moreover, low levels of cardiorespiratory fitness and muscle strength in children are associated with low bone mass, metabolic risk factors, cardiovascular diseases, and premature death in older age [19,20,21]. PF and intellectual maturity are linked from an early age, and can even predict intellectual maturity in 3–6-year-old children [22]. Furthermore, small improvements in children’s fitness are accompanied by significant improvements in cardiovascular health [23,24]. Above all, improvements in PF are likely to be important for the prevention of cardiovascular events in early years [25].

Physical exercise is one of the critical ways to achieve, maintain, and improve FMSs and PF, and the association between PA and health outcomes is also mediated by FMSs and PF [26,27,28]. However, two recent systematic and meta-analysis reviews suggested that the results of a physical exercise intervention on PF among preschoolers should be interpreted with care because of the relatively small number of randomized controlled trials (RCTs) pooled in each variable and the quality of RCTs [25,29]. Another two reviews on interventions to promote FMSs in childcare and kindergarten also expressed concern about the interpretation of the effectiveness of interventions to improve FMSs due to the high heterogeneity of comprehensive evidence and the lack of long-term follow-up [30,31]. Furthermore, longitudinal studies that address the interaction between FMSs and PF among preschoolers are scarce. Many types of physical exercise were used to intervene in FMSs and PF in preschool children, such as physical games, rhythmic activities, sports, basic movement activities, aerobic training, and comprehensive activities [25,31]. Based on the current evidence, we conclude that well-designed, organized physical exercise programs can improve FMSs and PF better than free play or unorganized physical activities in preschool children [25,31]. A variety of programs have been provided for the promotion of FMSs and PF in preschool children, but the characteristics of the different forms of physical exercise mean that their physical effects are different [32,33,34]. The comparability between different physical exercise programs is low and inadequate; thus, it cannot be concluded which type of physical exercise results in better improvement of FMSs and PF in preschool children according to current evidence. This is not conducive for kindergartens to be able to choose appropriate physical exercise programs. One study found that physical exercise programs with various forms and functions have certain advantages over rhythmic gymnastics and football activities in improving FMSs [35]. Another study found that Sports, Play, and Active Recreation for Kids (SPARK) courses can improve FMSs better than gymnastics and conventional physical activities in preschool children aged 4–6 years [33]. Therefore, the development of physical exercise programs for preschool children should improve the target of interest. Moreover, the effects of different forms of physical exercise on the FMSs and PF of preschool children still need to be further studied.

In China, young children (3–6 years old) population is 57 million, 81.7% of whom were enrolled in kindergarten in 2018. Children spend approximately 40 h each week in kindergarten [36]. However, there is little empirical evidence showing the effect of physical exercise on preschoolers’ FMSs and PF in China. Above all, the present trial is designed to respond to the theoretical and evidence gap. Therefore, the aims of this trial are to (1) determine the effectiveness of each of these physical exercise interventions in improving preschool children’s FMSs and PF; and (2) establish the differences between the effectiveness of different physical exercise programs on preschool children’s FMSs and PF. The research hypothesis is that physical exercise interventions will improve children’s FMSs and PF more than unorganized activities, and that MA will show larger beneficial effects than BA, RA, or BM on children’s FMSs and PF.

## 2. Methods

### 2.1. Study Design

The study is a single-blind, cluster-RCT study, with the kindergarten class as the cluster for the intervention. This study is a part of the Physical Exercise on FMSs and PF of preschoolers (PEFP) project. The PEFP project is a series of studies, including a cross-sectional survey (covering six provincial and municipal regions in China) and the aforementioned RCT (implemented in Putuo District, Shanghai, China). Preschoolers recruited from 5 kindergartens will be cluster-randomly allocated to 5 groups (i.e., four intervention groups and one control group). The intervention groups are (1) the BG group, consisting of football, basketball games, etc.; (2) the RA group, including cheerleading, rhythm exercise, etc.; (3) the BM group, consisting of different basic movements, such as walking, running, jumping, climbing, throwing, catching, etc.; and (4) the MA group, combination of all kinds of physical exercise that have been used in other intervention studies. The control group (control) is an unorganized PA group (Figure 1). The content of the intervention comes from previous research combined with consultation and interviews with preschool educators [7,37].

